# Androgen Deprivation therapy for Oligo-recurrent Prostate cancer in addition to radioTherapy (ADOPT): study protocol for a randomised phase III trial

**DOI:** 10.1186/s12885-022-09523-2

**Published:** 2022-05-02

**Keywords:** Oligometastasis, Recurrence, Prostate Cancer, MDRT, SBRT, ADT, PSMA PET/CT, Phase III

## Abstract

**Background:**

More than 60% of oligo-recurrent prostate cancer (PCa) patients treated with metastasis-directed radiotherapy (MDRT) develop biochemical recurrence within 2 years. This recurrence rate emphasises the need for improved treatment and patient selection. In line with the treatment of primary PCa, the efficacy of MDRT may be enhanced when combined with androgen-deprivation therapy (ADT). Furthermore, the availability of PSMA PET/CT offers an excellent tool for optimal patient selection for MDRT. This phase III randomised controlled trial will investigate the role of the addition of ADT to MDRT in oligo-recurrent PCa patients selected with PSMA PET/CT to enhance oncological outcome.

**Methods:**

Two hundred and eighty patients will be randomised in a 1:1 ratio to the standard treatment arm (MDRT alone) or the experimental arm (MDRT + 6 months ADT). Patients with biochemical recurrence after primary treatment of PCa presenting with ≤ 4 metastases will be included. The primary endpoint is the 2.5-year metastases progression-free survival (MPFS). Secondary endpoints are acute and late toxicity, quality of life, biochemical progression-free survival, overall survival, and the sensitivity of the PSMA PET/CT for detecting oligometastases at low PSA-levels. So far, between March 2020 and December 2021, one hundred patients have been included.

**Discussion:**

This phase III randomised controlled trial will assess the possible benefit of the addition of 6 months ADT to MDRT on metastases progression-free survival, toxicity, QoL and survival in PCa patients with 1–4 recurrent oligometastatic lesions.

**Trial registration:**

ClinicalTrials.gov, NCT04302454. Registered 10 March 2020.

**Supplementary Information:**

The online version contains supplementary material available at 10.1186/s12885-022-09523-2.

## Background

After primary treatment of prostate cancer (PCa), between 27 and 53% of all patients develop biochemical recurrence (BCR) within 10 years, and this is mostly due to metastatic disease [1, 2]. The prognosis of metastatic PCa is highly heterogeneous, with the number of metastases and location being important prognostic factors for PCa-specific mortality [3]. Several studies reported a potential survival benefit for patients treated with a limited number of metastases (i.e. oligometastases) [4, 5]. Yet, according to current EAU guidelines, the standard recommended treatment for patients with distant relapses (i.e. metastases) is long-term Androgen Deprivation Therapy (ADT) [1]. Long-term systemic treatment with ADT is not a curative treatment and is associated with multiple and significant side effects having a detrimental influence on quality of life [6]. Thus, the argument has been put forward to delay long-term implementation of ADT until metastases progression [1, 7]. Hence, there is a clear need for an early stage and stratified treatment targeting oligometastases aiming at longer progression-free survival of those patients. This need has been further emphasised since the introduction of prostate specific membrane antigen (PSMA) PET/CT scan. PSMA PET/CT scans have served to improve early detection of the recurrence site(s) in cases of BCR. Early detection of recurrence has led to a remarkable increase in the number of patients diagnosed with oligometastases [8–10].

Image-guided metastases-directed radiotherapy (MDRT) holds great promise to fulfil this need for early treatment [10–12]. While level 1 evidence and guidelines are lacking, MDRT is generally accepted as first treatment option for oligometastatic PCa patients. Up till now, two published randomized phase II trials (including 62 and 54 patients) reported a benefit of MDRT over a waiting policy [13, 14]. Still, > 60% of patients treated with MDRT develop BCR within 2 years after treatment [9, 11]. The reason could be twofold, either not all recurrence sites are detected or not all sites are treated sufficiently with MDRT. To eliminate potential (micro)metastases that are not (yet) visible and to enhance the therapeutic effect, we propose to combine targeted MDRT with a short course of (neo) adjuvant ADT. This approach has already been proven successful in primary treatment of high risk PCa reducing local recurrence, improving metastases progression-free survival and overall survival [15–17]. Moreover, we propose to improve and standardize patient selection using PSMA PET/CT. To our knowledge, this is the first study investigating the role of MDRT combined with ADT in oligo-recurrent PCa patients selected with the PSMA PET/CT.

## Methods/design

### Objectives

The primary aim of this project is to test the hypothesis that the addition of ADT to MDRT in well-selected PCa patients with oligometastatic disease prolongs the metastases progression-free survival (MPFS) compared to MDRT alone.

The secondary aim is obtaining more insight into the sensitivity of the PSMA PET/CT for detecting oligometastases at low PSA-levels.

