#### Inclusion criteria

Histologically proven initial diagnosis of adenocarcinoma of the prostate.Biochemical recurrence of prostate cancer following primary local prostate treatment (radical prostatectomy, primary radiotherapy or radical prostatectomy + prostate bed adjuvant/salvage radiotherapy).  BCR after surgery: PSA > 0.1 ng/ml.BCR after radiotherapy: PSA nadir + 2 ng/ml or 3 consequent rises in PSA level (after exclusion of possible bounce effect).Minimal 1 lesion and maximum 4 lesions (bone + lymph nodes) in total on PSMA PET/CT, without evidence of visceral metastases.Nodal relapse (N1) in the pelvis with a maximum of 4 positive lymph nodes. The upper limit of the pelvis is defined as the aortic bifurcation.Nodal relapse (M1a) above the aortic bifurcation with a maximum of 3 positive lymph nodes.Bone relapse with a maximum of 3 lesions.Combination of a, b, c with a maximum of 4 metastases.Age > 18 years.Recent PSMA PET/CT scan within 60 days prior to randomisation.PSA < 10 ng/ml.In case of chronic use of finasteride or dutasteride, the PSA value should be < 5 ng/ml.WHO performance state 0–2.Signed informed consent prior to registration/randomisation.

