### Primary endpoint

#### 2.5-year metastases progression-free survival (MPFS)

MPFS is defined as the time from randomisation to the date of metastases progression (appearance of new metastatic recurrence and/or progression of the treated metastases), reported by PSMA PET/CT during the follow-up (date PSMA PET/CT).

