### Secondary endpoints

#### Sensitivity of the PSMA PET/CT for detecting oligometastases and pattern of recurrences after MDRT

##### Biochemical Progression-Free Survival (bPFS)

bPFS is defined as the time from the date of randomisation to the date of biochemical (PSA) recurrence. In this study a PSA-value higher than the last value prior to therapy (validated 6 weeks later) is considered a secondary biochemical recurrence (post MDRT BCR).

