#### Imaging

Follow-up PSMA PET/CT should be performed in case of biochemical progression and for patients without progression at 12 and 24 months after treatment. Biochemical progression is defined as a PSA-value higher than the last value prior to therapy (validated 6 weeks later).

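### PSMA PET/CT sensitivity, a stated secondary aim, cannot be estimated at patient level because entry requires a positive scan; what the trial can report is a detection rate

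*Protocol article*

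**What the plan says.** The quantity appears in three places in the protocol article.

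- Objectives: "The secondary aim is obtaining more insight into the sensitivity of the PSMA PET/CT for detecting oligometastases at low PSA-levels".
- Abstract, Methods, among the secondary endpoints: "the sensitivity of the PSMA PET/CT for detecting oligometastases at low PSA-levels".
- Secondary endpoints, as a heading: "Sensitivity of the PSMA PET/CT for detecting oligometastases and pattern of recurrences after MDRT". The text that follows this heading defines biochemical progression-free survival, so the article gives the endpoint no definition of its own.

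The Inclusion criteria fix who can contribute. A patient needs "Minimal 1 lesion and maximum 4 lesions (bone + lymph nodes) in total on PSMA PET/CT", and the scan must be current: "Recent PSMA PET/CT scan within 60 days prior to randomisation". The only tissue requirement there is "Histologically proven initial diagnosis of adenocarcinoma of the prostate", which concerns the primary tumour and not the metastases.

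For follow-up, the primary endpoint takes metastatic progression as "reported by PSMA PET/CT during the follow-up (date PSMA PET/CT". The Imaging section says: "Follow-up PSMA PET/CT should be performed in case of biochemical progression and for patients without progression at 12 and 24 months after treatment". Table 2 lists no other imaging.

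**The concern.** Sensitivity is the share of truly diseased patients (or lesions) that the test finds. Its denominator includes those the test missed. This trial enrols only patients in whom the test has already found something, so at baseline the missed patients are absent from the data. The trial's own rationale expects disease that the scan does not show: the Background gives undetected recurrence sites as one possible reason for failure after MDRT, and invisible micrometastases as a reason for adding ADT.

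What is at stake is the meaning of a secondary result. A figure labelled as sensitivity would be fixed at 100% if computed per patient at baseline. Computed from follow-up scans without an independent standard, it would be a positivity rate under another name. Readers would take either as diagnostic accuracy. The treatment comparison is not at stake.

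**Working it through.** **The plan's own figures.** The article gives no number, precision target or hypothesis for this aim. Its sample size concerns MPFS only, and it reproduces:

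- Events (Schoenfeld, two-sided 5%, 80% power, HR 0.621): 4 × (1.960 + 0.842)² / (ln 0.621)² = 138.3, so 139.
- Dropout hazard from 18% at 30 months: g = −ln(0.82)/30 = 0.00661 per month.
- Probability of an observed event by 30 months: λ/(λ+g) × (1 − exp(−30(λ+g))). This gives 0.579 for λ = 0.0330 and 0.421 for λ = 0.0205, mean 0.500.
- Patients: 139 / 0.500 = 278, against 280 stated.

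So the sample size is sound for its own purpose and does not bear on the diagnostic aim.

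**Patient level, baseline.** Sensitivity = TP / (TP + FN). The entry rule sets FN = 0, so the apparent value is 280 / (280 + 0) = 100%. If the true sensitivity is s, the 280 enrolled correspond to 280/s patients with metastases, of whom 280/s − 280 had a negative scan and could not enter:

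| Assumed true sensitivity | Patients with metastases behind the sample | Missed, never enrolled | Apparent sensitivity in the trial |
|---|---|---|---|
| 40% | 700 | 420 | 100% |
| 60% | 467 | 187 | 100% |
| 80% | 350 | 70 | 100% |
| 95% | 295 | 15 | 100% |

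The four values of s are assumptions. The last column is the same in every row, so the trial's baseline data cannot distinguish between them. A larger sample would not help.

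**Lesion level, using later scans.** Suppose 1.5 lesions per patient are found at baseline and 0.5 to 1.0 further lesions per patient appear on later scans (assumed counts; the article gives none). Let q be the share of later lesions counted as already present but missed. Apparent lesion sensitivity is 1.5 / (1.5 + q × later lesions):

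| Later lesions per patient | q = 0 | q = 0.5 | q = 1 |
|---|---|---|---|
| 0.5 | 100% | 86% | 75% |
| 1.0 | 100% | 75% | 60% |

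The result depends on q, and a repeat of the same scan does not reveal q.

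**What can be estimated.** Follow-up scans can be negative, so a positivity rate is observable. As an illustration only, apply the Background's figure of more than 60% biochemical recurrence within 2 years to the 140 control patients: 0.60 × 140 = 84 PSA-triggered scans. At 50% positivity the 95% half-width is 1.96 × √(0.25/84) = 0.107, about ±11 points. This ignores dropout, borrows a recurrence rate whose definition may differ from the trial's trigger, and pools all PSA levels. In three equal PSA bands of 28 scans it would be 1.96 × √(0.25/28) = 0.185, about ±19 points.

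**The case against.** The best case for the plan is that the aim is worded softly, as gaining insight, with no hypothesis or accuracy threshold. The endpoint heading couples it with the pattern of recurrence after MDRT, which points to follow-up scans rather than baseline. A condensed article may also leave the definition and reference standard to the full protocol. Much of this stands, and it limits the point. It does not remove it, because the abstract lists sensitivity itself as an endpoint, and no text elsewhere could restore patients whom the entry rule excludes.

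Three stronger readings are tempting, and the documents do not support them.

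- *The scan is its own reference standard, so no form of sensitivity can ever be estimated.* The article names no reference standard at all. The primary endpoint defines an MPFS event, not a standard for this endpoint, and clinical progression-free survival counts progression on imaging without restricting it to PSMA PET/CT. The full protocol might name a standard usable at lesion level.
- *After a PSA rise with a negative scan, no later scan is due.* The Imaging section and the Table 2 footnote keep the 12- and 24-month scans for patients without progression, and do not say whether a PSA rise alone counts as progression there. They can be read as keeping those scans. A later scan would still not show whether a lesion was missed or new.
- *The trial will publish a false accuracy figure.* No passage commits to reporting a baseline sensitivity. The risk lies in the label, not in a stated analysis.

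**Conclusion.** The point holds at patient level. Entry on a positive PSMA PET/CT makes baseline false negatives 0 of 280 by rule, so the data carry no information on patient-level sensitivity in biochemical recurrence, at low PSA or otherwise. This follows from the inclusion criteria alone and needs no assumption about the full protocol.

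For follow-up the conclusion is narrower: with the imaging that the article schedules, missed and new lesions cannot be separated. That part rests on the article as shown and would weaken if the full protocol defines an independent standard. Even then, the figure would describe patients already selected by a positive scan and treated, some with ADT.

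This is a wrongly named secondary aim that should be corrected before analysis. It does not affect randomisation, MPFS, the sample size or the treatment comparison.

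**What to change.** In the abstract, the Objectives and the Secondary endpoints heading, replace sensitivity with: *PSMA PET/CT detection (positivity) rate by PSA level at the time of the follow-up scan, with 95% CI, and pattern of recurrence*.

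- Report it by arm, because ADT changes PSA and PSA triggers part of the scanning.
- Report scans triggered by biochemical progression separately from the scheduled 12- and 24-month scans. Restricting the rate to triggered scans would drop those done in patients without progression, which include the lower PSA levels that the aim is about.
- Make no statement about diagnostic accuracy.

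The cost is rewording in three places and a more modest secondary claim, with wide intervals within arm and PSA band. No new visits, scans or patients are needed. Keeping the word sensitivity would require far more: a defined reference standard and a cohort that includes scan-negative patients with biochemical recurrence, for example from a screening log.

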### Study design

The ADOPT-study is a multicentre open phase III randomised controlled trial. Participating centres are radiotherapy centres in the Netherlands (an updated list is available on ClinicalTrials.gov/ NCT04302454).

All eligible patients will be randomly assigned (1:1) to: MDRT alone (140 patients) versus MDRT + short term ADT (140 patients). (Fig. 1) Patients will be stratified by number of metastases, metastases organ (lymph nodes or bone, in case of both the bone group is applicable) and presence of local recurrence (identified on PSMA PET/CT).

**Fig. 1 Fig1:**
[figure not shown]
Study flowchart representing inclusion and follow-up

#### Inclusion criteria

Histologically proven initial diagnosis of adenocarcinoma of the prostate.Biochemical recurrence of prostate cancer following primary local prostate treatment (radical prostatectomy, primary radiotherapy or radical prostatectomy + prostate bed adjuvant/salvage radiotherapy).  BCR after surgery: PSA > 0.1 ng/ml.BCR after radiotherapy: PSA nadir + 2 ng/ml or 3 consequent rises in PSA level (after exclusion of possible bounce effect).Minimal 1 lesion and maximum 4 lesions (bone + lymph nodes) in total on PSMA PET/CT, without evidence of visceral metastases.Nodal relapse (N1) in the pelvis with a maximum of 4 positive lymph nodes. The upper limit of the pelvis is defined as the aortic bifurcation.Nodal relapse (M1a) above the aortic bifurcation with a maximum of 3 positive lymph nodes.Bone relapse with a maximum of 3 lesions.Combination of a, b, c with a maximum of 4 metastases.Age > 18 years.Recent PSMA PET/CT scan within 60 days prior to randomisation.PSA < 10 ng/ml.In case of chronic use of finasteride or dutasteride, the PSA value should be < 5 ng/ml.WHO performance state 0–2.Signed informed consent prior to registration/randomisation.

#### Exclusion criteria

Visceral metastases.PSA ≥ 10 ng/ml.PSA-doubling time ≤ 3 months.To measure the PSA-doubling time it is advised to use an online calculating tool. Hereby it is important to include all measurable PSA values after the primary therapy (i.e., prostatectomy or (salvage)radiotherapy).ADT or chemotherapy for recurrent PCa.Testosterone < 1.7 nmol/l.Painful metastases for which pain medication (> level 1) is indicated.Invasive active cancers other than superficial non-melanoma skin cancers.Inability or unwillingness to understand the information on trial-related topics, to give informed consent or to fill out QoL questionnaires.

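### Read literally, the PSA-doubling-time instruction brings the post-radiotherapy fall to nadir into the calculation, so rapidly doubling patients can pass the 3-month exclusion

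*Protocol article*

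**What the plan says.** The Exclusion criteria of the protocol article list "PSA-doubling time ≤ 3 months". Two sentences on the calculation follow: "To measure the PSA-doubling time it is advised to use an online calculating tool", and "Hereby it is important to include all measurable PSA values after the primary therapy (i.e., prostatectomy or (salvage)radiotherapy"). No tool or formula is named. No starting point at the nadir or at recurrence is set, and there is no time window.

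The Inclusion criteria admit three treatment histories: "radical prostatectomy, primary radiotherapy or radical prostatectomy + prostate bed adjuvant/salvage radiotherapy". Recurrence is defined separately by route. For surgery it is "BCR after surgery: PSA > 0.1 ng/ml". For radiotherapy it is "BCR after radiotherapy: PSA nadir + 2 ng/ml or 3 consequent rises in PSA level (after exclusion of possible bounce effect"). The Objectives describe the target population as "the addition of ADT to MDRT in well-selected PCa patients with oligometastatic disease".

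**The concern.** A doubling time describes how fast PSA is rising. After prostatectomy alone PSA is normally unmeasurable until relapse, so entering every measurable value enters only the rise. After primary radiotherapy PSA remains measurable on the way down, and after salvage radiotherapy it may do so. The article recognises this, because it anchors post-radiotherapy recurrence at the nadir and asks for bounce to be ruled out. The doubling-time instruction nevertheless names radiotherapy and starts the series before that nadir.

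A single slope fitted through a fall and a rise averages the two. The computed doubling time becomes long, or the slope turns negative and there is no doubling time, even when the relapse itself is fast. Whether the exclusion bites would then depend on treatment history rather than on PSA kinetics. Two of the three admitted histories include radiotherapy. At stake is whether the enrolled population is the one the threshold describes.

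**Working it through.** The article contains no worked doubling time, so there is no figure of its own to reproduce. Its sample size of 280 does not use doubling time as an input.

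**Inputs from the article:** the 3-month threshold; the values to be entered; recurrence after radiotherapy at nadir + 2 ng/ml or three rises; PSA below 10 ng/ml at entry.

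**Assumed:** all PSA series below, and the formula, doubling time = ln 2 / b, where b is the least-squares slope of ln(PSA) on months.

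**Step 1, one primary-radiotherapy series.** PSA is 3.0, 1.8, 1.2, 0.8, 0.6 and 0.5 at months 3, 6, 9, 12, 15 and 18, then rises from 0.5 at a fixed rate at months 21 and 24. There are eight values, the mean month is 13.5, and Σ(t − 13.5)² = 378.

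| True doubling time (months) | PSA at months 21, 24 | Σ(t − 13.5)(ln PSA − mean) | Slope b, all values | Result, all values | Result from nadir |
|---|---|---|---|---|---|
| 1.5 | 2.00, 8.00 | 6.718 | 6.718/378 = 0.01777 | 0.6931/0.01777 = 39.0 months | 1.5 months |
| 2.0 | 1.41, 4.00 | −3.160 | −0.0084 | not doubling | 2.0 months |
| 2.5 | 1.15, 2.64 | −9.086 | −0.0240 | not doubling | 2.5 months |

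In each row the last value exceeds nadir + 2 (0.5 + 2 = 2.5) and is below 10, so recurrence is met and the PSA ceiling is not breached. Adding a third rise to the 2.5-month row (6.06 at month 27) gives b = 0.01892 and 36.6 months. Waiting longer within the eligible PSA range does not repair the result.

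**Step 2, other assumed series, all with a true terminal doubling time of 2.5 months.**

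| History | Months | PSA | All values (months) | Terminal rise only (months) |
|---|---|---|---|---|
| Primary radiotherapy, fewer falling values | 3, 6, 12, 18, 21, 24, 27 | 2, 1.2, 0.6, 0.4, 0.92, 2.11, 4.85 | 27.6 | 2.5 |
| Salvage radiotherapy, measurable fall | 3, 6, 9, 12, 15, 18 | 0.3, 0.15, 0.1, 0.23, 0.53, 1.21 | 6.3 | 2.5 |
| Salvage radiotherapy, one early value, then undetectable | 3, 24, 27, 30 | 0.2, 0.2, 0.46, 1.06 | 15.6 | 2.5 |
| Prostatectomy alone, steady rise | 12, 15, 18, 21 | 0.10, 0.23, 0.53, 1.21 | 2.5 | 2.5 |
| Prostatectomy alone, slow then fast | 12, 18, 24, 30, 33, 36 | 0.10, 0.12, 0.15, 0.20, 0.46, 1.06 | 7.9 | 2.5 |

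**Step 3, a grid, so that nothing hangs on one series.** PSA falls log-linearly from 8 ng/ml to a nadir of 0.1, 0.3, 0.5 or 1.0 at 6, 12, 18 or 24 months, then doubles every 1, 1.5, 2, 2.5 or 3 months. It is measured quarterly and stopped before reaching 10. That makes 4 × 4 × 5 = 80 series, all of which meet the exclusion by construction. With all values entered, 39 have a zero or negative slope, 40 compute as more than 3 months (3.1 to 353.7), and 1 stays within the threshold (2.6). So 79 of 80 escape.

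**The case against.** The strongest reply is that the literal reading is not the only sensible one. The sentence may be meant to stop sites choosing two convenient values, and a clinician who has just established recurrence from the nadir may drop the falling values unprompted. A negative slope is also a visible non-answer and would prompt a second look. The tool is only advised, and least squares is an assumption. All of this is fair and limits what can be claimed about practice. It does not rescue the text, which stresses completeness, names radiotherapy and sets no start. Nor does it cover positive but badly inflated results such as 39 or 27.6 months, which look like ordinary answers.

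Three stronger readings are tempting, and the article does not support them.

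- *The article tells sites to enter the fall.* It never mentions the fall. That follows from the literal wording and is not stated.
- *Fast-doubling patients have been enrolled.* The section on the first 100 patients gives arm, number and site of metastases and local recurrence. It does not give primary treatment, PSA kinetics or the values used.
- *The trial result is biased.* Eligibility is settled before randomisation and applies to both arms alike. Both arms receive metastasis-directed radiotherapy, and nothing in the article shows that these patients would respond differently to the added androgen deprivation.

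The salvage case is also less certain than primary radiotherapy. The parenthesis can be read as starting the series after salvage treatment, and the result varies widely with the series assumed (6.3 against 15.6 months).

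**Conclusion.** The point holds as a defect in the eligibility wording. For patients with measurable falling values after radiotherapy, the instruction taken literally makes the 3-month exclusion close to inoperative under a log-linear calculator. True doubling times of 1.5 to 2.5 months became 39 months or no doubling in the lead series, and 79 of 80 grid series escaped. Prostatectomy-only patients with a steady rise are classified correctly; in that group the computed value is too long only if the rise accelerates.

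The size rests on assumed PSA series and an assumed formula, and it varies with the length of the fall, the nadir and the spacing of measurements. The number of patients affected cannot be known from the article. The consequence is for the composition of the trial population and generalisability. The between-arm comparison and the sample-size calculation stand.

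**What to change.** Reconcile the instruction with its own threshold and with the nadir-based recurrence definition in the Inclusion criteria. Suggested wording: *Enter every measurable PSA value belonging to the current rise, from the nadir after the most recent local therapy up to randomisation. Do not enter undetectable values, values from the falling phase, or values that precede the most recent local therapy.*

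The restriction to measurable values must stay. Assume a post-prostatectomy nadir at month 3, then 0.12 ng/ml at month 24 with a true doubling time of 2.5 months at months 26, 28 and 30. The measurable values give 2.5 months. Entering the undetectable nadir as 0.01 gives 4.8 months, and as 0.05 gives 8.7 months. Starting simply at the nadir would thus create the same error in the group now handled correctly.

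For patients already randomised (100 of 280 at the time of the article), recompute doubling time this way from the recorded PSA history and report how many were at or below 3 months. Keep them all in the analysis.

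The cost is one sentence in the eligibility section and the screening form, made during recruitment, plus a recalculation from existing data. A few patients now admitted would be excluded, and some doubling times would rest on fewer values. The wording does not address a slow-then-fast rise after prostatectomy alone.
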